# Effect of Daikenchuto (TJ-100) on gastrointestinal symptoms following laparoscopic colectomy in patients with colon cancer: study protocol for a randomized controlled trial

**DOI:** 10.1186/s13063-017-2307-7

**Published:** 2017-11-21

**Keywords:** TJ-100, Laparoscopic colectomy, Postoperative gastrointestinal symptoms

## Abstract

**Background:**

Postoperative paralytic ileus can be a difficult complication for both surgeons and patients. Causes and treatments have been discussed for more than two centuries, but have not yet been fully resolved. Daikenchuto (TJ-100, DKT) is a traditional Japanese herbal medicine. Recently, some beneficial mechanisms of DKT to relieve paralytic ileus have been reported. DKT can suppress inflammation, increase intestinal blood flow, and accelerate bowel movements. Therefore, we have designed a randomized controlled trial to investigate the effects of DKT on postoperative gastrointestinal symptoms following laparoscopic colectomy in patients with left-sided colon cancer at a single institution.

**Methods/design:**

As primary endpoints, the following outcomes will be evaluated: (i) grade of abdominal pain determined using the numeric rating scale (NRS), (ii) grade of abdominal distention determined using the NRS, and (iii) quality of life determined using the Gastrointestinal Quality Life Index (GIQLI). As secondary endpoints, the following will be evaluated: (i) postoperative nutritional status (Onodera’s Prognostic Nutritional Index (PNI) and the Controlling Nutritional Status score (CONUT score)), (ii) duration to initial flatus, (iii) duration to initial defecation, (iv) bowel gas volume, (v) character of stool (Bristol Stool Form Scale), (vi) defecation frequency per day, (vii) postoperative complications (Clavien-Dindo classification), (viii) length of postoperative hospital stay, and (ix) metabolites in the stool and blood. This trial is an open-label study, and needs to include 40 patients (20 patients per group) and is expected to span 2 years.

**Discussion:**

To our knowledge, this is the first randomized controlled trial to investigate the effects of DKT on postoperative subjective outcomes (i.e., postoperative quality of life) following laparoscopic colectomy as primary endpoints. Exploratory metabolomics analysis of metabolites in stool and blood will be conducted in this trial, which previously has only been performed in a few human studies. The study aims to guide a future full-scale pragmatic randomized trial to assess the overall effectiveness of DKT to improve the postoperative quality of life following laparoscopic colectomy.

**Trial registration:**

UMIN-CTR (Japan), UMIN000023318. Registered on 25 July 2016.

**Electronic supplementary material:**

The online version of this article (doi:10.1186/s13063-017-2307-7) contains supplementary material, which is available to authorized users.

## Background

Postoperative paralytic ileus can be a difficult complication for both surgeons and patients. Causes and treatments have been discussed for more than two centuries, but have not yet been fully resolved [1]. The incidence of postoperative ileus following colectomy is reported to be at least 10%, and is considered to be inevitable for patients undergoing abdominal surgeries [2]. Patients who suffer from postoperative ileus require additional treatments such as fasting, antibiotics, decompression tubes, or even surgical intervention for suspected bowel strangulation. Owing to this, hospital stays lengthen and medical costs can increase more than 15% [2]. Therefore, the prevention of postoperative ileus is crucial for surgeons.

Daikenchuto (TJ-100, DKT) is a traditional Japanese herbal medicine (Kampo). This medicine is a crude drug extract and consists of four active components including processed ginger, ginseng, Japanese zanthoxylum peel and koi (maltose powder). In Japan, DKT has been clinically used for the treatment of postoperative paralytic ileus [3]. Recently, some beneficial mechanisms of DKT to relieve paralytic ileus have been reported. DKT can suppress inflammation, increase intestinal blood flow, and accelerate bowel movements [4–7]. The anti-inflammatory effect is derived from inhibited activity of cyclooxygenase-2 and upregulation of endogenous adrenomedullin [4, 5]. An increase in intestinal blood flow is due to upregulation of calcitonin gene-related peptide [6]. Accelerated bowel movement is due to adjustment of the contraction and relaxation of the intestine by release of acetylcholine, nitric oxide and other excitatory neurotransmitters [8]. Therefore, DKT is considered to be a potential drug to reduce postoperative paralytic ileus and improve postoperative quality of life for patients with colon cancer.

## Methods/design

### Objective

The aim of this study is to assess the effect of DKT on postoperative gastrointestinal symptoms following laparoscopic colectomy in patients with left-sided colon cancer.

### Study design and setting

This study will be conducted at Kyoto University Hospital in Japan, and the design is an open-label randomized controlled trial. This study is expected to span a period of 2 years. Perioperative procedures in both groups will be performed based on the clinical path for laparoscopic colectomy in Kyoto University Hospital. All patients will receive standard bowel preparation (75 mg sodium picosulfate and 12 mg pursennid) and antibiotic prophylaxis (oral doses of 1 g kanamycin and 750 mg metronidazole), and surgical procedures will be conducted by well-experienced, board-certified laparoscopic colorectal surgeons at our institution. Except for the administration of DKT, treatment protocols including perioperative management and surgical procedures will be congruent among the intervention group (DKT group) and the control group (non-DKT group).

### Endpoints

The following primary endpoints will be evaluated in this clinical trial: (i) grade of abdominal pain determined using the numeric rating scale (NRS), (ii) grade of abdominal distention determined using the NRS, and (iii) quality of life determined using the Gastrointestinal Quality Life Index (GIQLI) [9]. NRS measurements of abdominal pain and distention will be taken prior to surgery and at postoperative days (POD) 1, 4, 7, 14 and 28. GIQLI will be taken before surgery and at POD 14 and 28.

The secondary endpoints are (i) postoperative nutritional status (Onodera’s prognostic nutritional index (PNI) [10] and Controlling Nutritional Status score (CONUT score) [11]), (ii) time to initial flatus, (iii) time to initial defecation, (iv) bowel gas volume measured using analysis software, (v) character of stool (Bristol Stool Form Scale [12]), (vi) defecation frequency per day, (vii) postoperative complications (Clavien-Dindo classification [13]), (viii) duration of postoperative hospital stay, and (ix) metabolomics analysis of metabolites in stool and blood using gas chromatography-tandem mass spectrometry (GC/MS/MS) and liquid chromatography-tandem mass spectrometry (LC/MS/MS) (Fig. 1).

**Fig. 1 Fig1:**
[figure not shown]
Schedule of enrolment, intervention, and assessments. GIQLI, Gastrointestinal Quality Life Index

### Eligibility criteria

The eligible patients must satisfy the criteria defined below. Potential participants who meet the inclusion criteria will be recruited at outpatient clinics or during preoperative visits before surgery.

Inclusion criteria:Patients with left-sided colon cancer (including recto-sigmoid cancer) who are scheduled to undergo laparoscopic surgeryClinical stage I, II and IIIPatients who suffer from abdominal pain and distention at POD 1 (NRS score ≥1)The European Cooperative Oncology Group (ECOG) performance status of 2 or less.Patients aged 20 years and older at registrationPatients who can take medications orallyWritten informed consent provided to participate in the study

Exclusion criteria:Patients who have history of abdominal surgery or history of bowel obstructionPatients with concomitant inflammatory bowel disease such as ulcerative colitis and Crohn’s diseasePatients with concomitant endometriosisPatients requiring emergency surgeryPatients who have been or will be treated by chemotherapy or radiotherapyPatients with severe comorbidity such as cardiac disease, liver disease, pulmonary disease or renal diseasePatients who took Japanese herbal medicine (Kampo) up to 4 weeks prior to registrationPatients who took gastrointestinal prokinetic drugs, antipsychotic drugs or antidepressant drugs up to 4 weeks prior to registrationPatients with a history of a Kampo allergy in other formulationsPatients with hepatitis B or CPatients who are unable to take medications orally at POD 1Patients who are unsuitable for study inclusion as determined by the investigator (e.g., those with severe dementia)

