### Registration

Patients will be enrolled at POD 1. An eligibility report form will be sent to the registration center (APO PLUS STATION Co., Ltd, Tokyo, Japan). Eligible patients will be centrally randomized to either the DKT group or non-DKT group at the registration center using a computer random number generator with the minimization method for TNM stage, tumor location, and age. Information on the necessary follow-up evaluations will then be sent from the registration center. A flow diagram of this study is shown in Fig. 2.

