**Fig. 2 Fig2:**
[figure not shown]
Study flow chart. Investigators obtain informed consent from eligible patients before surgery. Patients are enrolled in the trial, if they can take medicine orally and have abdominal pain and/or distention at postoperative day (POD) 1. Enrolled patients are randomly assigned to either the Daikenchuto (DKT) or non-DKT group

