### Statistical analysis

All analyses will be performed under the intention-to-treat principle. However, patients will be excluded from the analyses if they are proved to be ineligible after enrollment. Both primary and secondary endpoints will be compared between the DKT group and the non-DKT group. A two-tailed *P* value less than 0.05 is considered statistically significant. For continuous variables, the *t* test will be used when continuous variables follow a normal distribution, whereas the Wilcoxon rank-sum test will be used when continuous variables follow a non-normal distribution. For categorical variables, the chi-square test or Fisher’s exact test will be used according to the cell count.

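### The POD 1 symptom rule is given as both symptoms in one place and either symptom in another, so a one-symptom patient could be randomised under one wording and excluded under the other

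*Protocol article*

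**What the plan says.** The Eligibility criteria section makes its list binding: "The eligible patients must satisfy the criteria defined below". One inclusion item admits patients "who suffer from abdominal pain and distention at POD 1 (NRS score" of at least 1). The legend to Fig. 2 describes entry differently: "Patients are enrolled in the trial, if they can take medicine orally and have abdominal pain and/or distention at postoperative day (POD) 1". It gives no NRS threshold.

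The Registration section fixes the timing, "Patients will be enrolled at POD 1", and says that an eligibility report form goes to the registration centre, which then randomises. Under Treatment methods, study medication starts on POD 2.

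The entry symptoms are also outcomes. The Endpoints section lists among the primary endpoints "i) grade of abdominal pain determined using the numeric rating scale (NRS), (ii) grade of abdominal distention determined using the NRS", with NRS scores taken before surgery and on POD 1, 4, 7, 14 and 28.

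The Statistical analysis section says "All analyses will be performed under the intention-to-treat principle", and then that "patients will be excluded from the analyses if they are proved to be ineligible after enrollment".

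**The concern.** The two statements define different populations. The difference is not one of detail: joining the symptoms with an and, or with an and/or, changes who may be randomised. Three features make it more than a drafting slip.

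- The symptom rule is applied on POD 1 and is, with oral intake, the condition that the legend names for enrolment. It is the gate to randomisation.
- Its two symptoms are two of the three primary endpoints. Under the either-symptom rule, some patients enter with a score of 0 on one primary scale. Under the both-symptoms rule, everyone enters with at least 1 on each. The baseline distributions of the primary outcomes therefore depend on which rule is used.
- The analysis section permits removal after enrolment for ineligibility. With two rules in print, a one-symptom patient accepted under the legend can afterwards be judged ineligible under the list. The trial is open-label, and the article does not say that this judgement is made without knowledge of the arm.

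At stake are the balance that randomisation provides and, if such patients were removed, part of the sample size.

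**Working it through.** **Comparison of the two rules.** Apply both to POD 1 scores, taking the list literally and taking a symptom as present in the legend when its NRS score is at least 1 (the legend gives no threshold of its own).

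| Pain | Distention | List: both | Legend: either |
|---|---|---|---|
| ≥1 | ≥1 | eligible | eligible |
| ≥1 | 0 | not eligible | eligible |
| 0 | ≥1 | not eligible | eligible |
| 0 | 0 | not eligible | not eligible |

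The rules disagree only on one-symptom patients. Each rule is itself well defined. What is missing is a statement of which applies.

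**The plan's own sample size.** Inputs from the Sample size determination section: GIQLI difference 20, SD 20, power 80%, two-sided 5%, dropout 20%.

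- Per group: n = 2 × (1.960 + 0.842)² × (20/20)² ≈ 15.7, rounded up to 16, so 32 in total. This reproduces.
- With dropout: 32 / (1 − 0.20) = 40. This reproduces.
- Power at 16 per group: 80.7% by the normal approximation and 78.1% by the exact t-test (noncentral t, 2n − 2 degrees of freedom, noncentrality √(n/2) at a difference of 1 SD).

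**Conditional illustration.** The share of enrolled patients with only one symptom is not in the article. Take it as 0%, 10% or 30% (assumed). Suppose that all of them are removed as ineligible, that none is replaced, and that the full 20% dropout applies to the rest. Patients per group are rounded down.

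| Share removed | Removed of 40 | Left after 20% dropout | Per group | Exact power at 1 SD |
|---|---|---|---|---|
| 0% | 0 | 40 × 0.8 = 32 | 16 | 78.1% |
| 10% | 4 | 36 × 0.8 = 28.8 | 14 | 72.1% |
| 30% | 12 | 28 × 0.8 = 22.4 | 11 | 60.7% |

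The 20% allowance is stated for dropout only. A 20% removal for ineligibility would by itself take 40 to 40 × 0.8 = 32 and use up the whole allowance. These figures concern GIQLI, on which the trial was sized. The article gives no basis for a corresponding calculation on the NRS scales.

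**The case against.** The strongest answer is that the criteria list is the operative text and the legend only condenses it, since it omits the NRS threshold and most other criteria. On an ordinary reading the list would govern. The authors may also have used the word and loosely, because one NRS threshold follows both symptoms. Either may be so, but the article does not say which, and the legend's and/or does not abbreviate the list's condition: it is a different condition.

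Second, one eligibility form goes to one centre before allocation. If that form applied a single rule consistently, no randomised patient changes status and nothing is lost. This stands. The form is not shown, so later exclusion is a possibility. A reader might infer that the investigators intend to drop one-symptom patients; nothing in the article supports that. The exclusion clause is also open to question whatever the entry wording; the point here is only that the conflict gives it something to act on.

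Third, the power figures rest on an assumed share and a worst-case chain of events. This stands too, and it is why zero loss belongs in the table.

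Fourth, a reader might conclude that a patient scoring 0 on POD 1 tells us nothing about that scale. That is too strong. The endpoint is the grade of the symptom at the scheduled visits, not improvement from POD 1. Such a patient cannot fall below 0 but can develop the symptom later, so the arms can still differ. The threshold of 1 also leaves scores close to the floor under the both-symptoms rule.

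**Conclusion.** The contradiction is certain: the Eligibility criteria section and the legend to Fig. 2 give different answers for a patient with one symptom on POD 1, and no other section resolves it. It should be corrected because the rule decides who is randomised, involves two of the three primary endpoints, and meets an exclusion clause that acts after enrolment in an open-label trial.

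It does not follow that the trial population is undefined. It is ambiguous between two defined rules, which differ only on one-symptom patients.

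The consequence for power is conditional and cannot be sized from the article. It ranges from no loss, if one rule was used throughout, to a fall from about 78% to about 72% or 61% if 10% or 30% were removed in addition to full dropout. Those shares are assumptions and should not be read as an expected loss.

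**What to change.** 1. Reconcile the inclusion item, the legend to Fig. 2 and the registration centre's eligibility form so that all three carry the same rule. Which rule it should be is for the investigators to say. Recruitment has run since September 2016, so they should check what the form in use has actually required.
2. State in the Statistical analysis section that no patient already randomised is excluded from the analysis because of the differing wording.
3. Analyse each NRS endpoint with its own POD 1 score as a covariate. That score is already collected, and it precedes treatment, which starts on POD 2. This adjusts for baseline differences between patients; it does not remove a floor effect. If the analysis plan already provides for it, nothing further is needed.

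The cost is a wording amendment, a check of one form and a sentence or two on the analysis. The planned sample size, the treatment and the data collected do not change. It should be settled before the data are analysed.

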### Sample size determination

The sample size calculation is based on a primary endpoint, GIQLI. The GIQLI questionnaire containing 36 questions each with five response categories. The responses to questions are summed to give a numerical score (0–128 points). A previous report [9] indicates that the mean ± standard deviation (SD) change in the GIQLI score between two measurements before and 2 weeks after laparoscopic cholecystectomy in 194 patients was 17 ± 20.7 points. Therefore, the clinically significant mean difference in the GIQLI score is set at 20 with a SD of 20. Using a power level of 80% and a two-sided significance level of 5%, 32 patients (16 patients in each group) are required to show a difference between the DKT and non-DKT groups. Therefore, we determined that 40 patients (20 patients in each group) are needed to endure 20% dropout of patients from this trial.

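### An exclusion for future chemotherapy or radiotherapy has no time anchor; combined with removal of patients found ineligible after enrolment, its literal wording lets a post-randomisation decision take patients out of an intention-to-treat analysis

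*Protocol article*

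**What the plan says.** All of the relevant text is in the protocol article.

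- **Eligibility criteria.** Clinical stages I to III may enter. Patients "who have been or will be treated by chemotherapy or" radiotherapy may not. The future part has neither a time window nor a qualifier such as planned at registration. Other items in the same list are anchored: the Kampo and the prokinetic, antipsychotic and antidepressant exclusions look back 4 weeks from registration, and inability to take oral medication is judged at POD 1.
- **Registration.** "Patients will be enrolled at POD 1". An eligibility form goes to the registration centre, and eligible patients are then randomised "with the minimization method for TNM stage, tumor location, and age".
- **Endpoints.** "GIQLI will be taken before surgery and at POD 14 and 28". The pain and distention ratings also end at POD 28.
- **Statistical analysis.** "All analyses will be performed under the intention-to-treat principle". The next sentence makes an exception: "patients will be excluded from the analyses if they are proved to be ineligible after enrollment".
- **Sample size determination.** For the Gastrointestinal Quality Life Index (GIQLI), "the clinically significant mean difference in the GIQLI score is set at 20 with a SD of 20". This gives 16 patients per group, raised to 20 per group for 20% dropout.

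**The concern.** Most eligibility criteria are facts already fixed when the patient is registered. If one of them turns out to have been violated, removing the patient departs from strict intention-to-treat, but the reason at least predates allocation. A criterion about what will happen later, with no end date, is different. Read literally, it can become false after randomisation, and the analysis rule then removes the patient. Even treatment first started after POD 28, when the GIQLI, pain and distention assessments are complete, would qualify.

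The trial is open-label, so such a decision would be taken by people who know the allocation. If it also depended on how the patient recovered, removal would be related to outcomes: complications and nutritional status are themselves secondary endpoints. The randomised comparison could then be biased in either direction. The number analysed would also fall in a trial whose Discussion already lists possibly insufficient sample size among its limitations.

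**Working it through.** **1. The rules side by side**

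| Rule | Section | Timing |
|---|---|---|
| Clinical stage III admitted | Eligibility criteria | Before surgery or at registration |
| Future chemotherapy or radiotherapy excluded | Eligibility criteria | Open-ended |
| Enrolment, then randomisation | Registration | POD 1 |
| Last GIQLI and symptom ratings | Endpoints | POD 28 |
| Patients proved ineligible are dropped | Statistical analysis | Any time after enrolment |

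Two readings are possible.

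- *Literal:* the criterion fails if treatment is ever given. A decision after POD 1 makes a randomised patient ineligible, and the analysis rule removes that patient.
- *Planned at registration:* the criterion is settled at POD 1. Only patients whose existing plan was overlooked could later be found ineligible, and later decisions play no part.

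The article does not say which is meant.

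**2. The plan's own sample size**

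Inputs from Sample size determination: difference 20, SD 20, power 80%, two-sided 5%.

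n per arm = 2 × (1.960 + 0.842)² × (20/20)² = 15.7, so 16 per arm and 32 in total. Allowing for dropout, 32 / 0.8 = 40. The stated figures reproduce.

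Power at 16 per arm is 80.7% by the normal approximation and 78.1% by the noncentral t. The t-test figure is the baseline below.

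**3. Illustrative size under the literal reading**

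The stage III share (s) and the fraction of those patients later treated (c) are not in the document. Assumed ranges: s = 20-40%, c = 50-90%. Every treated patient is assumed to have been enrolled and then removed.

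- Removed = 40 × s × c: low case 40 × 0.2 × 0.5 = 4.0; high case 40 × 0.4 × 0.9 = 14.4.
- Left before other losses: 36.0 and 25.6.

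*(a) Full 20% dropout on top of the removals.* Multiply by 0.8: 28.8 and 20.5 patients, or 14.4 and about 10.2 per arm.

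*(b) Removals counted within the 8-patient allowance (40 − 32).* Low case: 4 removals leave room for 4 other losses, so 32 remain. High case: 14.4 exceeds 8, so with no other dropout 25.6 remain, or 12.8 per arm.

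| Case | Per arm | t-test power (difference 20, SD 20) |
|---|---|---|
| Plan after 20% dropout | 16 | 78% |
| (a) low | 14.4 | 73% |
| (a) high | 10.2 | 57% |
| (b) low | 16 | 78% |
| (b) high | 12.8 | 68% |

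These figures cover loss of numbers only. The possible bias cannot be sized from the document.

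**The case against.** The strongest reply is that the criterion has an ordinary reading that causes no trouble. Eligibility is reported once, before randomisation. On that footing the future part refers to treatment planned at that time, and being proved ineligible means that a failure already present at registration was found later. The article describes no re-check of eligibility against later chemotherapy and no symptom or GIQLI assessment beyond POD 28; Monitoring provides only for an eligibility check in a sample of 10 patients. A clinical stage III patient with no planned treatment can meet both criteria, and minimising on stage shows only that stage is expected to vary. The article also condenses a fuller protocol, which may define the term.

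Much of this stands, and it rules out three stronger inferences that a reader might draw.

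- *Stage III admission contradicts the exclusion.* It does not; both can be satisfied.
- *The criterion cannot be settled at POD 1.* This needs knowledge of when and how chemotherapy decisions are made, and the document is silent on that.
- *Randomised patients will be lost, and power will fall to 73-57%.* No removal procedure is described, some such patients might be screened out at registration, the shares are assumed, and the article does not say whether removals fall outside the dropout allowance.

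The reply does not dispose of the wording itself. The point is not only absent detail: the article states an open-ended criterion and an open-ended removal rule next to an intention-to-treat commitment. Introducing the removal rule openly as an exception does not limit it to facts that predate randomisation. The harmless reading is plausible, but nothing in the text requires it.

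**Conclusion.** The point holds as an exposure created by the wording of the eligibility criterion and the analysis rule together, not as a demonstrated loss of patients. Applied literally, the two rules let a decision made after randomisation, with allocation known, remove a patient from an analysis described as intention-to-treat. Read as planned at registration, they do not.

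The size is unknown. Under the assumed shares, with every treated patient removed, the loss is 4 to 14 of 40. Power is about 73-57% if full dropout is added, or between no loss against plan and about 68% if removals use the dropout allowance first. Outcome-related removal is possible but not shown, because the document does not say what such treatment decisions depend on. The correction is worth making because it is cheap and does not depend on these numbers.

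**What to change.** Two wording changes.

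1. **Statistical analysis (the more important).** State that a randomised patient may be declared ineligible only on facts that existed before randomisation, judged without knowledge of allocation. Add that patients whose chemotherapy or radiotherapy is decided after enrolment stay in the intention-to-treat analysis.
2. **Eligibility criteria.** Word the exclusion as treatment already given or already planned at registration (POD 1), and reconcile it explicitly with the admission of clinical stage III. Whether to add a time window, such as POD 28, is for the investigators to settle.

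Neither change needs extra patients, visits or procedures, and the planned 40 stands. Recruitment is already under way, so the analysis sentence should be fixed before any outcome comparison by arm. The downside is that a few analysed patients may start chemotherapy before the last visit. This can be recorded, with its start date, and examined in a sensitivity analysis.
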